
### fMRI experimental design and auditory paradigm

2.4

We chose a mixed block/event-related design (Figure 3) in which trials of auditory stimuli are interspersed with blocks of silence of varying durations (15 blocks in total, each lasting 45 s and containing 30 trials on average). This design allows for the simultaneous modelling of the transient, trial-related activity, and the sustained, task-related BOLD activity. That is, by alternating silence blocks with task blocks (i.e., blocks with trials with auditory stimuli) we can optimize the sensitivity for discriminating events within trials and all events combined within a block. Blocks with only standard events will be alternated with blocks containing both standard and deviant events. Standard and deviant blocks will alternate in pseudorandomized order (ABBA…), in which no more than two identical types of blocks can follow one another. The length of the silence blocks will be randomized in 1-s steps in intervals of 7–10 s. Based on previous studies (Bekinschtein et al., 2009), each event (both standard and deviant sounds) will lasts 0.05 s; inter-stimulus interval (ISI) will be fixed at 0.1 s and inter-trial interval (ITI) will be jittered in 0.05-s steps between 0.7 to 1 s. We will use a variant of the “classic oddball” paradigm (Figure 3), in which trials will consist of a randomized number of repetitions (i.e., 3–5) of standard events plus one deviant event. Standard sounds will have a frequency of 100 Hz and deviants of 500 Hz. The total length of the auditory stimulation will be 15 min. Each task block will last 45 s (to have both a frequency still below the recommended 128 s high-pass filter, but also a reasonable number of trials). The parameters selected for the auditory stimulation are the result of the efficiency and collinearity analyses we performed to optimize the efficiency of our design. Sounds will be delivered via a Serene Sound Digital MRI-compatible system.

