### Efficiency and collinearity analyses for optimizing the auditory paradigm to fMRI

2.5

With the following analyses, we sought to maximize the efficiency of the auditory paradigm which led to the protocol described in the section “fMRI experimental design and auditory paradigm.” Estimation of the efficiency can be defined as “a measure of the reliability with which model parameters are estimated”(Mechelli et al., 2003). The efficiency of a design strongly “affects the sensitivity with which experimental effects are detected” (Mechelli et al., 2003). In order to find the (*a priori*) most efficient design to detect our effects of interest, we manipulated the temporal distribution of events, resulting in several designs whose efficiency was estimated *a priori* and then compared. The variables manipulated were the length of the silence blocks (i.e., randomized in 1-s steps in intervals of 7–20 s, 7–10 s, 15–20 s, 10–15 s), the ordering of standard and deviant blocks (i.e., interleaved order or pseudorandomized order in which no more than two identical types of blocks can follow one another), the type of oddball paradigm. We selected four different types of oddball paradigms for comparing their efficiency, of which only one was chosen for the experiment. In the “classic oddball” paradigm (Squires et al., 1975), trials consist of four standard sounds and one deviant, where the deviant is defined by a change in frequency. The “roving oddball” (Garrido et al., 2007) differs with each trial presenting sounds of the same frequency and starting a new trial with a different frequency, making the first event of a trial a deviant. We also designed two “mixed oddballs,” in which trials follow the “classic oddball” rule but with the difference that the number of repetitions of standard events is randomized, between three and five (“Mixed Oddball35”) or between three and seven repetitions of standards (“Mixed Oddball37”). The efficiency analysis was conducted by comparing all possible combinations of parameters (i.e., ISI, ITI, stimulus and block duration) for the different oddball paradigm designs. Please note that the efficiency calculation is related to the number of scans (i.e., to a given TR and duration of experiment), and specific to a given contrast. We calculated the efficiency for TR = 0.842 s, 900 s duration of the experiment and for the following three contrasts: main effect of the standard response, main effect of the deviant response and the difference between standard and deviant responses. For more information on how we computed efficiency, see our repository on GitHub “Efficiency-Analysis-fMRI-mixed-design,” where each step of the analysis is detailed: https://doi.org/10.5281/zenodo.8117861. In addition to the efficiency analysis, we also performed a collinearity analysis in SPM to estimate the extent to which our two events (standard and deviant) were collinear (i.e., whether their responses correlated with each other)—see our GitHub repository for more details on how to compute collinearity in SPM. The design that was most efficient and with least collinearity was the “Mixed Oddball35” with 7–10 s silence blocks and pseudorandomized order (mean efficiency for the difference between standard and deviant events = 0.843). As depicted in Figure 4, “Mixed Oddball35” was found to have comparable efficiency with the “Classic oddball” (mean efficiency for the difference between standard and deviant events = 0.845). We chose the “Mixed Oddball35” for the experiment as randomizing the number of repetitions of the standard sounds has the advantage of decreasing expectation.

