
**Figure 4 fig4:**
[figure not shown]
Efficiency results for four auditory paradigms. Results shown are for contrast standard-deviant, TR = 0.842 and for an experiment duration of 900 s (i.e., 1,125 scans). Efficiency values are reported for “Classic oddball,” “Mixed Oddball35,” “Mixed Oddball37,” and “Roving oddball” with silence blocks of duration 7–10 s and in pseudorandomized order (ABBA). Whiskers corresponds to approximately +/−2.7σ and 99.3 percent coverage. We selected the “Mixed Oddball35” for its combination of high efficiency and the reduction of expectation achieved through the randomization of standard sounds.

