### Preprocessing and statistical analysis

2.9

As we will use a mixed block/event-related design, all the following analyses (see Table 1 for a summary) will be conducted on the BOLD time-series at both the block and trial level: for the block-level analyses, we will contrast (1) task blocks (i.e., standard and deviant blocks combined) with silence blocks and (2) standard vs. deviant blocks. For the trial-level analysis, we will contrast (1) combined deviant and standard trials with BOLD extracted time-series of simulated time points during silence blocks and (2) deviant vs. standard trials. For the purpose of this project and the hypotheses presented, the analysis of RS data will not be discussed in this study.

**Table 1 tab1:** Hypotheses tested and corresponding analyses. This table provides a comprehensive overview of the analyses, brain areas, atlas employed, and statistical methods used for each hypothesis tested in this study.

Hypotheses tested	Analyses	Considered brain areas	Atlas	Statistical analysis
*Hypothesis 1*	Activation analysis (ROI-based)	All 7 sub-thalamic regions (L/R)	Oxford thalamic connectivity atlas	Small volume correction
*Hypothesis 2*	Activation analysis (ROI-based)	Primary auditory cortex (L/R): Heschl’s gyrus	Harvard-Oxford cortical and subcortical structural atlases	Small volume correction
*Hypothesis 3*	Activation analysis (ROI-based)	Secondary regions (L/R): superior temporal gyrus (both anterior and posterior division)	Harvard-Oxford cortical and subcortical structural atlases	Small volume correction
*Hypothesis 4*	ROI-to-ROI based connectivity	2 sub-thalamic (sensory and temporal) nuclei and Heschl’s gyrus	Oxford thalamic connectivity atlas/ Harvard-Oxford cortical and subcortical structural atlases	Subject-level: wGLM Group-level: LME
*Hypothesis 5*	ROI-to-ROI based connectivity	Heschl’s gyrus and superior temporal gyrus (both anterior and posterior division)	Harvard-Oxford cortical and subcortical structural atlases	Subject-level: wGLM Group-level: LME
*Hypothesis 6*	Voxel-to-voxel connectivity	Whole cortical and subcortical brain matters	No atlas	Subject-level: Intrinsic connective analysis Group-level: LME

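### The auditory run's block count, length and scan count do not agree, and a 128-s high-pass filter in the activation model would on average remove about half of the standard-vs-deviant block contrast

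*Protocol article*

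**What the plan says.** All references are to the protocol article.

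- **Section 2.4, timing.** The design has "15 blocks in total, each lasting 45 s and containing 30 trials on average". For the silences, "The length of the silence blocks will be randomized in 1-s steps in intervals of 7–10 s". For the whole run, "The total length of the auditory stimulation will be 15 min".
- **Section 2.4, order.** "Standard and deviant blocks will alternate in pseudorandomized order", illustrated as ABBA followed by an ellipsis, with no more than two blocks of the same type in succession.
- **Section 2.4, block length.** The 45-s choice is explained as being "to have both a frequency still below the recommended 128 s high-pass filter" while giving a reasonable number of trials.
- **Section 2.5.** "We calculated the efficiency for TR = 0.842 s, 900 s duration of the experiment". Three contrasts were scored: the standard response, the deviant response and their difference. The section says that efficiency depends on the number of scans and on the contrast. Interleaved and pseudorandomized orders were both candidates, and the pseudorandomized design was chosen.
- **Figure 4 caption.** Results are given for TR 0.842 and "for an experiment duration of 900 s (i.e., 1,125 scans". The order is labelled ABBA.
- **Section 2.6.** The acquisition TR is 842 ms.
- **Section 2.9.** The second of the two planned block-level contrasts is "2) standard vs. deviant blocks".

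**The concern.** Two things look wrong.

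First, the stated blocks and silences do not fill the stated run, and the stated scan count does not match the stated TR. Section 2.4 rests the stimulus parameters on the efficiency analysis, and Section 2.5 ties that analysis to the scan count. A reader therefore needs to know which run was scored and which will be delivered.

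Second, a 45-s block passes a 128-s filter when the comparison is sound against silence, because that cycle is one block plus one silence. Standard against deviant blocks is a slower comparison: its cycle spans at least two blocks, and four under ABBA. A high-pass filter treats such slow variation as drift and removes it. At stake is the precision of one of the two planned block-level contrasts, for which Section 2.5 reports no efficiency.

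**Working it through.** **1. Run length (inputs from Section 2.4).** Task time is 15 × 45 = 675 s. The number of silences depends on whether the run starts or ends with one.

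| Silences | at 7 s | at 8.5 s (mean) | at 10 s |
|---|---|---|---|
| 14 | 773 s | 794 s | 815 s |
| 15 | 780 s | 802.5 s | 825 s |
| 16 | 787 s | 811 s | 835 s |

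Against 900 s, between 900 − 835 = 65 s and 900 − 773 = 127 s have no assigned content. The plan's 30 trials per block do reproduce. An average trial has five sounds of 0.05 s, four gaps of 0.1 s and a mean inter-trial interval of 0.85 s, so 0.25 + 0.40 + 0.85 = 1.5 s, and 45 / 1.5 = 30. The mismatch therefore lies in block count, silence length or total length.

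**2. Scan count (Sections 2.5 and 2.6, Figure 4).** 900 / 0.842 = 1,069, against 1,125 stated, which is about 5% too many. Conversely, 1,125 × 0.842 = 947 s. The stated figure equals 900 / 0.8 exactly, so it fits TR 0.8 s. The spectral windows in Section 2.9.6 fit 0.842 s: 50, 100 and 200 s give 59.4, 118.8 and 237.5 volumes, against 60, 118 and 238 stated. At 0.8 s they would be 62.5, 125 and 250.

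**3. Cycle lengths against the filter.** The 128-s cut-off is 1/128 = 0.0078 Hz.

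- Task vs silence: 45 + 8.5 = 53.5 s, which passes.
- Standard vs deviant blocks, interleaved: 2 × 53.5 = 107 s (0.0093 Hz), which passes.
- Standard vs deviant blocks, strict ABBA: 4 × 53.5 = 214 s (0.0047 Hz), below the cut-off.

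**4. How much is removed.** The standard-minus-deviant block regressor was convolved with a double-gamma haemodynamic response and sampled at 0.842 s. A discrete-cosine drift set was then projected out. The run had 15 blocks within 900 s and silences drawn from 7–10 s. "Random" covers all 1,440 near-balanced orders with at most two identical blocks in a row.

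| Order | Variance kept, 128 s | Standard error vs interleaved | Variance kept, 256 s |
|---|---|---|---|
| Interleaved | 92% | 1 | 98% |
| Random, at most two in a row | 46% on average (5th–95th percentile about 33–67%) | about 1.4 | 87% |
| Strict ABBA | 29% | about 1.8 | at least 90% |

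More than half the variance is lost in about 73% of the random orders. If the run ends with the last block (about 815 s), that share is 67%, the random orders keep 47% on average, and the other two rows change by only a few points. The ratios follow from the shares: √(92/46) = 1.41 and √(92/29) = 1.78.

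**The case against.** The order is defined by a run-length rule, and ABBA carries an ellipsis. A literal fixed ABBA would be neither pseudorandom nor in need of such a rule. This stands: the random-order result is the main one, and strict ABBA is the worse case if the Figure 4 label is meant literally. A reader might infer that most of the contrast is lost in every run. The documents do not support that, since the loss across admissible orders ranges from about 7% to 74%.

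The 128-s filter is called recommended when block length is explained, but Section 2.9.2, on the activation model, states no cut-off. Only the connectivity pipeline fixes one (0.008 Hz), and block-weighted correlations are not affected in the same way. This also stands, so the filter point is conditional.

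The scope is narrow. Of four planned contrasts (two block-level, two trial-level), one is harmed. Hypothesis 6, on deviant against standard processing, is tested through voxel-to-voxel connectivity, not this activation contrast.

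A reader might also infer that the efficiency values were computed for a different run. That is not shown. Section 2.5 and the caption both state TR 0.842 s, and 1,125 appears once, in a parenthesis that may be a slip. The code is in a repository that is not among the documents, so whether it used 1,125 scans, or already includes a high-pass filter, cannot be told from here. A scan-count error common to all candidate designs would probably change their ranking little.

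Finally, Section 2.5 compared interleaved order and preferred the pseudorandomized design for efficiency and low collinearity. That deserves respect, but the reported scores (0.843 and 0.845) are for standard and deviant events and do not settle the block contrast. Section 2.2 gives the run as approximately 15 min, which softens the timing mismatch; the 900 s in Section 2.5 does not.

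**Conclusion.** The timing inconsistency holds under every reading tried: 773–835 s against 900 s, and 1,069 scans against 1,125.

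The filter point holds conditionally. If a 128-s cut-off is used in the activation model, the standard-vs-deviant block contrast loses on average about 54% of its regressor variance under the constrained random order (standard error about 1.4 times interleaved), and about 71% (1.8 times) under literal ABBA. These figures assume a canonical haemodynamic response, a discrete-cosine filter and near-equal block numbers. The standard-error ratios come from regressor variance alone, without a noise model. Task-vs-silence blocks and the trial-level contrasts are not pushed below the filter by the block order.

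This should be corrected, but it does not undermine the design as a whole.

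**What to change.** 1. Reconcile block count, silence length, run length and scan count in Section 2.4, Section 2.5 and the Figure 4 caption.
2. Confirm which scan count the efficiency code used. Rerun the efficiency and collinearity analysis with 1,069 scans, the high-pass filter and the standard-vs-deviant block contrast included, for the order actually used. This costs a rerun of existing code.
3. State the cut-off for the activation model in Section 2.9.2, then choose one of two routes:
   - **Interleave blocks in runs not yet acquired.** One example is 16 blocks, eight per type, with 17 silences: 720 + 17 × 7 = 839 s to 720 + 17 × 10 = 890 s. This fits within 900 s and keeps about 93% of the contrast variance at 128 s. It needs a stimulus-script change and no extra scanner time. The cost is a predictable block order, although the 3–5 randomization within trials remains. The text should say that interleaved order was among the candidates in Section 2.5 but that no block-contrast score was reported.
   - **Keep the order and prespecify a longer cut-off.** At 256 s, random order keeps about 87%. This also serves runs already acquired. The cost is more low-frequency drift left in the data.

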**Figure 3 fig3:**
[figure not shown]
Schematic representation of the mixed block/event-related design (top) and of the “Mixed35” oddball rule (bottom). White musical notes denote standard sounds, black notes deviant sounds. Created with BioRender.com.

### Efficiency and collinearity analyses for optimizing the auditory paradigm to fMRI

2.5

With the following analyses, we sought to maximize the efficiency of the auditory paradigm which led to the protocol described in the section “fMRI experimental design and auditory paradigm.” Estimation of the efficiency can be defined as “a measure of the reliability with which model parameters are estimated”(Mechelli et al., 2003). The efficiency of a design strongly “affects the sensitivity with which experimental effects are detected” (Mechelli et al., 2003). In order to find the (*a priori*) most efficient design to detect our effects of interest, we manipulated the temporal distribution of events, resulting in several designs whose efficiency was estimated *a priori* and then compared. The variables manipulated were the length of the silence blocks (i.e., randomized in 1-s steps in intervals of 7–20 s, 7–10 s, 15–20 s, 10–15 s), the ordering of standard and deviant blocks (i.e., interleaved order or pseudorandomized order in which no more than two identical types of blocks can follow one another), the type of oddball paradigm. We selected four different types of oddball paradigms for comparing their efficiency, of which only one was chosen for the experiment. In the “classic oddball” paradigm (Squires et al., 1975), trials consist of four standard sounds and one deviant, where the deviant is defined by a change in frequency. The “roving oddball” (Garrido et al., 2007) differs with each trial presenting sounds of the same frequency and starting a new trial with a different frequency, making the first event of a trial a deviant. We also designed two “mixed oddballs,” in which trials follow the “classic oddball” rule but with the difference that the number of repetitions of standard events is randomized, between three and five (“Mixed Oddball35”) or between three and seven repetitions of standards (“Mixed Oddball37”). The efficiency analysis was conducted by comparing all possible combinations of parameters (i.e., ISI, ITI, stimulus and block duration) for the different oddball paradigm designs. Please note that the efficiency calculation is related to the number of scans (i.e., to a given TR and duration of experiment), and specific to a given contrast. We calculated the efficiency for TR = 0.842 s, 900 s duration of the experiment and for the following three contrasts: main effect of the standard response, main effect of the deviant response and the difference between standard and deviant responses. For more information on how we computed efficiency, see our repository on GitHub “Efficiency-Analysis-fMRI-mixed-design,” where each step of the analysis is detailed: https://doi.org/10.5281/zenodo.8117861. In addition to the efficiency analysis, we also performed a collinearity analysis in SPM to estimate the extent to which our two events (standard and deviant) were collinear (i.e., whether their responses correlated with each other)—see our GitHub repository for more details on how to compute collinearity in SPM. The design that was most efficient and with least collinearity was the “Mixed Oddball35” with 7–10 s silence blocks and pseudorandomized order (mean efficiency for the difference between standard and deviant events = 0.843). As depicted in Figure 4, “Mixed Oddball35” was found to have comparable efficiency with the “Classic oddball” (mean efficiency for the difference between standard and deviant events = 0.845). We chose the “Mixed Oddball35” for the experiment as randomizing the number of repetitions of the standard sounds has the advantage of decreasing expectation.

**Figure 4 fig4:**
[figure not shown]
Efficiency results for four auditory paradigms. Results shown are for contrast standard-deviant, TR = 0.842 and for an experiment duration of 900 s (i.e., 1,125 scans). Efficiency values are reported for “Classic oddball,” “Mixed Oddball35,” “Mixed Oddball37,” and “Roving oddball” with silence blocks of duration 7–10 s and in pseudorandomized order (ABBA). Whiskers corresponds to approximately +/−2.7σ and 99.3 percent coverage. We selected the “Mixed Oddball35” for its combination of high efficiency and the reduction of expectation achieved through the randomization of standard sounds.

### MRI data collection

2.6

MRI data will be collected with a 3 T Magnetom Prisma Fit scanner (Siemens, Erlangen, Germany) equipped with a 20-channel array receiver head–neck coil. For rs-fMRI and task based-fMRI, the scanning parameters will be as follows: echo-planar imaging (EPI) with multi-band acceleration factor of 6, 7/8 phase partial Fourier, 2.25 mm slice thickness, no gap between slices, 2.25 mm x 2.25 mm in-plane spatial resolution, 842 ms repetition time (TR), 30 ms echo time (TE), 52° flip angle, 207 mm x 225 mm field of view (FOV) and a matrix size of 92 × 100. For anatomical reference, a high-resolution T1-weighted image will be acquired for each subject during the awake session (T1-weighted 3D magnetization-prepared rapid gradient echo (MPRAGE) sequence, TR = 1900 ms, TE = 2.19 ms, inversion time (TI) = 900 ms, sagittal orientation, 224 slices, 1 mm slice thickness, FoV = 256×240 mm^2^, matrix size = 256x240x224, voxel size = 1x1x1 mm^3^, GRAPPA R = 2 acceleration factor in phase-encoding direction (AP).

### Variables of interest, randomization, and blinding

2.7

In this experiment, the dependent variable will be the BOLD signal (during RS/task sessions). The independent variables will be both the connected/disconnected condition and the type of sounds delivered, i.e., standard or deviant events or silence. The connected/disconnected condition cannot be randomized, given its unpredictability, i.e., it is impossible to predict which individuals will report being connected and which will report being disconnected. In contrast, several parameters of the auditory paradigm will be randomized (e.g., the number of repetitions of standard events). Similarly, the temporal order of the waking and sedation sessions cannot be randomized given the use of anesthetics: data acquisition after the end of sedation would in fact correspond more to acquiring data during the recovery than during the awakening phase. Finally, the order of the RS and task sessions will not be randomized due to time constraints: since the collection of reports must occur immediately after the task session, if the task preceded the RS session, we would be forced to collect reports after the task and then wait for the participants to lose responsiveness again to acquire the 10 min of rs-fMRI, considerably extending acquisition time. Data preprocessing and analysis will be performed blind to the conditions of the experiment.

